#### Data collection

IPCP quizzes will be completed by all participants before and after the training to assess their knowledge improvement, while attitude and perception of IPCP will only be assessed after the training, using the Jefferson Scale of Attitudes Toward Interprofessional Collaboration (JeffSATIC) [66] and the Perception of Interprofessional Collaboration Model Questionnaire (PINCOM-Q) [67]. The ICP training process will be documented by RA to describe the participants’ responses. The following information regarding progress of implementation will be monitored and recorded: date of the first patient-reported to PI or co-researchers, implementation of IPCP, consultation request, and clinical meeting [65]. A modified McMaster Ottawa Scale [63] will be used by the co-researchers to observe IPCP in delivering care to pregnant women with heart diseases. In this stage the total number of pregnant women with cardiac disease will be recorded including detailed information regarding their identity, diagnosis, and level of facilities used during their prenatal, antenatal, and post-natal care. Observations will be conducted for every pregnant woman with heart diseases in the study setting to evaluate the intended and unintended outcome of the ICPs, to determine the progress made and learning from the actions using participatory tools such as progress markers, photos, and videos [68–70]. The intended outcomes include improvement of interprofessional communication, and patient outcomes such as length of stay and readmission [68, 69], whereas the unintended outcomes consist of interprofessional knowledge gaps, tension, and disrupted positive communication [70]. All health professionals and patients will be asked to provide consent before being photographed or videotaped.

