#### Participants

All health professionals, representative of the municipality health office, co-researchers and clinical consultants who contribute in designing the model will be involved in training activity, while the ongoing monitoring will only involve health professionals who implement the ICPs and co-researchers in their health facilities. The PI and co-researchers will provide ongoing monitoring and consultation throughout the implementation of ICPs.

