#### Analysis

The score of IPCP quizzes will be compared using a paired t-test to determine training effectiveness. The attitude, perception and implementation toward IPCP will be analysed descriptively and classified based on their profession and workplaces. All qualitative data from observations dan field notes will be gathered and analysed with the data from subsequent stage.

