**Planning stage**					
ICPs development	Agreed ICPs	Review of source	–		Principal investigator
		Consensus: Delphi method	JEFFSATIC PINCOM-Q Modified McMaster Ottawa Scale Audio recording	Attitude and Perception of IPCP on developing ICPs	Senior community obstetrician and cardiologist. The liaison officers The representatives of municipality health office. The representatives of the BPJS Senior health professionals

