**Implementation stage**					
IPCP implementation	Description of IPCP implementation using ICPs	One day training of ICPs and IPCP implementation	IPCP quiz JEFFSATIC PINCOM-Q Audio-visual recording	Participant responses	All health professionals, representative from the municipality health office, co-researchers and consultant who contribute in designing the model
		Medical record review Observation	Modified McMaster Ottawa Scale	Collaborative Communication Share leadership conflict resolution Team functioning Role and responsibility	All health professionals who use the ICPs

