## Discussion

IPCP has been hypothesized to improve health outcome through enhancing interprofessional communication, resources utilization efficiency and patient safety [27, 76]. This study will provide comprehensive information about the benefits of, success and barrier factors of IPCP for pregnant woman with heart diseases referral care. This study implements and evaluates the IPCP in the primary, secondary to tertiary health care facilities and develops ICPs as a tool to enhance IPCP through defining a clear role and responsibilities of each health professionals based on their workplace. Perception, attitude, and experience of both health professionals and patients will be determined during the process.

To our knowledge, this will be the first study on IPCP involving multi-level maternal health services in Indonesia. It is expected to produce significant evidence on the improvement of IPCP on maternal referral care for pregnancy with heart diseases, the third leading indirect cause of maternal mortality [77]. The PAR study design will engage health professionals in all four stages (need assessment, planning, implementation, and evaluation) [78]. It will improve IPCP understanding, which will lead to better professional habits, mindset changes, and discipline to effectively implement IPCP [79]. Findings from this study will inform health service planner and policymaker to strengthen the practice of IPCP during the referral process. Thus, its implementation is expected to provide high-quality care for pregnant women with heart diseases as the long term impact.

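### JeffSATIC and PINCOM-Q are scheduled only after training, so no change in their scores can be estimated, and Table 3 contradicts that timing

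*Protocol article*

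**What the plan says.** In Stage 3, under Data collection, knowledge is measured twice: "IPCP quizzes will be completed by all participants before and after the training to assess their knowledge improvement". The same sentence treats the two questionnaires differently: "while attitude and perception of IPCP will only be assessed after the training", using JeffSATIC for attitude and PINCOM-Q for perception.

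The Stage 3 Analysis follows that split. For knowledge, "The score of IPCP quizzes will be compared using a paired t-test to determine training effectiveness". Attitude and perception are summarised descriptively by profession and workplace.

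Table 3 gives a different schedule. In the planning stage, the Delphi row lists "JEFFSATIC PINCOM-Q Modified McMaster Ottawa Scale Audio recording" as instruments, with the variable "Attitude and Perception of IPCP on developing ICPs". In the implementation stage, the training row lists "IPCP quiz JEFFSATIC PINCOM-Q Audio-visual recording".

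The Discussion says of the study: "It is expected to produce significant evidence on the improvement of IPCP on maternal referral care". It also expects better understanding of IPCP to lead to a change in mindset.

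**The concern.** A single score taken after training has nothing to be compared with. If staff score well on JeffSATIC or PINCOM-Q, the training may have helped, or they may have held those views already. The planned breakdown by profession and workplace does not separate the two.

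The timing is an explicit choice about data collection, and it cannot be repaired afterwards: once staff are trained, the baseline is lost. The conflict with Table 3 adds a practical problem, because those running the study cannot tell from the protocol whether the scales are to be given in Stage 2, and to whom.

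At stake is whether the study's two named quantitative measures of attitude and perception can support any statement about improvement.

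**Working it through.** The protocol states no sample size, power or precision for these scales, so there is no figure of its own to reproduce. The check has two parts.

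**1. Assessments per instrument, by source**

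| Instrument | Source | Before training | After training | Within-person change |
|---|---|---|---|---|
| IPCP quiz | Stage 3 text | 1 | 1 | Estimable for all trainees |
| JeffSATIC, PINCOM-Q | Stage 3 text | 0 | 1 | Not estimable |
| JeffSATIC, PINCOM-Q | Table 3 | 1 (Delphi participants only) | 1 | Estimable only for Delphi participants who also attend training |

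- Stage 2 comes before training, because the training delivers the pathways agreed in Stage 2. The Table 3 listing in the planning stage is therefore a pre-training assessment.
- The Stage 2 text on the consensus process names only the modified McMaster Ottawa Scale. The Stage 2 Analysis covers that scale, the progress of agreement and the qualitative data. It neither names nor analyses the two questionnaires, so Table 3 conflicts with the Stage 2 text as well.
- Stage 4 lists only interviews and FGDs, so it adds no scale scores.
- Stage 4 also says the four stages repeat over four cycles. It does not say that the training or the scales are repeated. If they were, the first administration under the Stage 3 text would still follow training.
- Under neither reading does the protocol plan an analysis of change in these scales.

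**2. What a baseline would buy**

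Staff in Table 1 (midwives + nurses + physicians + obstetricians + cardiologists):

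- SAI: 25 + 15 + 15 + 8 + 7 = 70
- DRP: 6 + 5 + 10 + 5 + 0 = 26
- PHC A: 6 + 6 + 5 = 17
- PHC B and PHC C: 4 + 4 + 4 = 12 each
- Total: 70 + 26 + 17 + 12 + 12 = 137

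This is an upper bound for the groups in Table 1. SAI's 15 physicians equal its 8 obstetricians plus 7 cardiologists, so specialists may be counted twice. If they sit within physicians at both hospitals, the total is 137 − 15 − 5 = 117. Not all of these staff need be trainees, since training is for those who manage these patients.

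The 95% CI half-width for mean change, in SD units of a single score with equal SD before and after, is t(0.975, n−1) × √(2(1−r)) / √n, where r is the pre/post correlation. The protocol gives no r. The middle value is an assumption and the outer columns show its range.

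| Completers n | r = 0.3 | r = 0.5 | r = 0.7 |
|---|---|---|---|
| 100 | 0.23 | 0.20 | 0.15 |
| 117 | 0.22 | 0.18 | 0.14 |
| 137 | 0.20 | 0.17 | 0.13 |

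For n = 100 and r = 0.5: 1.984 × 1.000 / 10 = 0.198 SD. The figure of 100 completers is illustrative. With post-training scores alone there is no estimate of change at any n.

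**The case against.** The strongest reply is that the scales are declared descriptive. None of the four specific objectives concerns change in a scale score, and on attitude and perception the Discussion promises only that they will be determined during the process. The improvement it expects concerns practice in referral care. This stands: the plan contains no invalid analysis of these scales.

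The Table 3 conflict can also be softened. The word only in Stage 3 may merely contrast the scales with the quiz, and the Delphi row may be an additional use with its own variable. That is possible, but the Stage 2 text does not support it, so the passages still need reconciling.

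Two stronger readings are tempting, and the documents support neither.

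- A reader might infer that the study can show no change in attitude or perception at all. Stage 1 interviews and FGDs cover both topics before training, Stage 4 interviews and FGDs follow it with analysis mirroring Stage 1, and the modified McMaster Ottawa Scale is used in Stages 2 and 3. Qualitative and observational before/after evidence exists. The gap is confined to the scale scores.
- A reader might infer from "co-researchers and clinical consultants who contribute in designing the model will be involved in training activity" that people who helped design the model dilute the paired quiz comparison and should be left out. Nothing shows that contributing to a cardiac pathway raises pre-training knowledge of IPCP, and the protocol gives no count of such people from which a dilution could be worked out. Co-researchers are midwives in their own workplaces, and excluding Delphi participants sits poorly with a participatory design.

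**Conclusion.** The point holds for the scale scores. Under the Stage 3 text, JeffSATIC and PINCOM-Q have no baseline, so within-person change in them cannot be estimated. Under Table 3, a baseline would exist for Delphi participants alone. The two schedules contradict each other, and the Stage 2 text matches the Table 3 planning row neither in instruments nor in analysis.

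This is a design limitation with a cheap remedy plus an internal contradiction, not an error in a planned analysis. It matters because these scales are the study's named quantitative measures of attitude and perception, and the Discussion looks forward to improvement and a change in mindset. The achievable precision, about ±0.17 to ±0.20 SD for 137 down to 100 completers, rests on an assumed correlation of 0.5, equal SDs and near-complete participation by the Table 1 staff. The missing baseline depends on none of these assumptions.

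**What to change.** - Give JeffSATIC and PINCOM-Q to all trainees at the existing pre-training quiz session as well as after training.
- Report mean within-person change with a 95% CI, alongside the planned description by profession and workplace. Label it change after training, since there is no control group.
- Reconcile the Stage 3 data collection text and the Stage 2 text with Table 3. If the scales are also wanted in the Delphi stage, say so in Stage 2, state who completes them and how the scores will be summarised. If not, remove them from that row.
- If no baseline is added, state that the two scales are descriptive only and support no claim of change.

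The cost is two further questionnaires at a session that already takes place, so some added participant time, plus edits to the text and Table 3. The change has to be made before training begins.

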#### Analysis

The score of IPCP quizzes will be compared using a paired t-test to determine training effectiveness. The attitude, perception and implementation toward IPCP will be analysed descriptively and classified based on their profession and workplaces. All qualitative data from observations dan field notes will be gathered and analysed with the data from subsequent stage.

### Stage 4: evaluation stage

This stage will focus on the formal evaluation after the three previous stages have been completed.

#### Participants

The participants in this stage will be to those health professionals and patients who participate in the ongoing monitoring activity during stage three.

#### Data collection

Interviews and FGDs will be conducted to assess both on being involved in a study using PAR (such as degree of participation and learning gained on ICPs and IPCP throughout the study) and the IPCP implementation outcome such as acceptability, appropriateness, adoption, feasibility, and implementation cost [71–73]. The interviews will be conducted with obstetricians, cardiologists and patients. For the FGD, four FGDs will be conducted with physicians working in primary care and hospitals, as well as midwives in all types of health facilities and hospital nurses. Each group will consist of 6–10 participants. All four stages will be applied to 5 patients for each cycle and will be repeated until four completed cycle of PAR.

#### Analysis

All data collected in this stage will be analyzed mirroring the analysis in stage one.

A summary of data collection in all four stages is illustrated in Table 3.

**Table 3 Tab3:** Data collection activities in each stage of the study

Stages	Outcome	Data collection activities	Instrument	Variable	Participant
**Diagnostic stage**					
Determine local context of existing IPCP in maternal referral services for pregnancy with heart diseases	Policy factors Organizational factors Team factors Individual factors	Medical record review (obstetric cases in 2017)	Collecting document form	Existing referral system and IPCP	Medical record
		In-depth interviews and Focus group discussions (FGDs)	Interview and FGD guideline Audio recording	Contributing factor in IPCP implementation	Heads of obstetrics and gynaecology, and cardiology Person in charge (PIC) of maternal referral from each health care facility. Patients
**Planning stage**					
ICPs development	Agreed ICPs	Review of source	–		Principal investigator
		Consensus: Delphi method	JEFFSATIC PINCOM-Q Modified McMaster Ottawa Scale Audio recording	Attitude and Perception of IPCP on developing ICPs	Senior community obstetrician and cardiologist. The liaison officers The representatives of municipality health office. The representatives of the BPJS Senior health professionals
**Implementation stage**					
IPCP implementation	Description of IPCP implementation using ICPs	One day training of ICPs and IPCP implementation	IPCP quiz JEFFSATIC PINCOM-Q Audio-visual recording	Participant responses	All health professionals, representative from the municipality health office, co-researchers and consultant who contribute in designing the model
		Medical record review Observation	Modified McMaster Ottawa Scale	Collaborative Communication Share leadership conflict resolution Team functioning Role and responsibility	All health professionals who use the ICPs
**Evaluating stage**					
Evaluation and improvement of IPCPs implementation	ICPs refinement	In-depth interview	Audio recording. Interview and FGD guideline	Implementation outcome: Acceptability Appropriateness Adoption Feasibility Implementation cost	All health professionals, co-researchers and patient/family who employ the ICP in patient management
		FGDs			

### Trustworthiness

Natural situations should be examined in qualitative studies to ensure natural, evidence-based, prolonged engagement that has built trust and rapport in the participants [74]. The first author is the principal investigator of this study and a female physician who has been working at the tertiary hospital where the study will be conducted. She visits the primary and secondary care facilities on a regular basis and is therefore familiar with all the health professionals working at these facilities. Prior to data collection activities, all participants will be approached through face to face interaction in their workplace. Participants were aware that this research is part of her dissertation project to improve maternal services for pregnant women with cardiac diseases through applying ICPs implementation. All participants have appropriate understanding of the study purpose and their roles prior to engagement in this study.

ICPs will be implemented in this study through training, ongoing monitoring and consultation. Therefore, it is likely that others may be present besides the participants and researcher. For example the patient’s family and administration staff. At the beginning of this research, in-depth interviews, FGDs and document analysis will be conducted to summarize the results of the context and situation analysis. Data collected in each stage will be shared with previous and subsequent participants to encourage full participation. ICPs and IPCP training will be held to promote the involvement of all participants in the ICPs implementation [75]. Data from the medical record reviews will be triangulated with observations, in-depth interviews and FGDs results. All interviews and FGDs will be audio-recorded and transcripts will be confirmed by informants through peer debriefing and member checking. A thick description will be produced to provide behavioural, cultural and contextual findings, thus allowing the research to be readily replicated [74].

## Discussion

IPCP has been hypothesized to improve health outcome through enhancing interprofessional communication, resources utilization efficiency and patient safety [27, 76]. This study will provide comprehensive information about the benefits of, success and barrier factors of IPCP for pregnant woman with heart diseases referral care. This study implements and evaluates the IPCP in the primary, secondary to tertiary health care facilities and develops ICPs as a tool to enhance IPCP through defining a clear role and responsibilities of each health professionals based on their workplace. Perception, attitude, and experience of both health professionals and patients will be determined during the process.

To our knowledge, this will be the first study on IPCP involving multi-level maternal health services in Indonesia. It is expected to produce significant evidence on the improvement of IPCP on maternal referral care for pregnancy with heart diseases, the third leading indirect cause of maternal mortality [77]. The PAR study design will engage health professionals in all four stages (need assessment, planning, implementation, and evaluation) [78]. It will improve IPCP understanding, which will lead to better professional habits, mindset changes, and discipline to effectively implement IPCP [79]. Findings from this study will inform health service planner and policymaker to strengthen the practice of IPCP during the referral process. Thus, its implementation is expected to provide high-quality care for pregnant women with heart diseases as the long term impact.

The study may face some potential methodological and practical challenges. The study setting is limited to one tertiary hospital and its referral network, the patient population and the service within which we are seeking to implement this pathway. This could limit the generalizability of findings to other hospitals with different characteristics. Further adaptations may be required to implement similar efforts in Regional public hospitals. In terms of PAR, participation is the key to success. We are aware that time constraints and workload of each participant may vary, but we are confident that intense communication during training, monitoring and continuous discussions could improve participants’ contribution in this study [80–82]. Concerning potential biases due to the role of the first author in the hospitals, her familiarity and long experiences working in the study setting may be useful to deepen the understanding gained from the interview/FGDs.

## Data Availability

The datasets generated and analysed during the current study will be included in the subsequent publication of the results.

## Abbreviations

BEmNOC: Basic Emergency Obstetric Care
CEmNOC: Comprehensive Emergency Obstetric Care
COREQ: COnsolidated criteria for REporting Qualitative research
DRP: Demak Regional Public
FGD: Focus Group Discussion
ICD: International Classification of Diseases
ICPs: Integrated Care Pathways
ICU: Intersive Care Unit
IPCP: Interprofessional Collaboration Practice
MMR: Maternal Mortality Rate
PAR: Participatory Action Research
PHC: Public Health Centre
PI: Principal Investigator
PIC: Person in charge
RA: Research Assistant
SAI: Sultan Agung Islamic
